## Abstract

**Background:**

Delirium is an acute state of brain dysfunction characterised by fluctuating inattention and cognitive disturbances, usually due to illness. It occurs commonly in the intensive care unit (ICU), and it is associated with greater morbidity and mortality. It is likely that disturbances of sleep and of the day-night cycle play a significant role. Melatonin is a naturally occurring, safe and cheap hormone that can be administered to improve sleep. The main aim of this trial will be to determine whether prophylactic melatonin administered to critically ill adults, when compared with placebo, decreases the rate of delirium.

**Methods:**

This trial will be a multi-centre, randomised, placebo-controlled study conducted in closed ICUs in Australia. Our aim is to enrol 850 adult patients with an expected ICU length of stay (LOS) of 72 h or more. Eligible patients for whom there is consent will be randomised to receive melatonin 4 mg enterally or placebo in a 1:1 ratio according to a computer-generated randomisation list, stratified by site. The study drug will be indistinguishable from placebo. Patients, doctors, nurses, investigators and statisticians will be blinded. Melatonin or placebo will be administered once per day at 21:00 until ICU discharge or 14 days after enrolment, whichever occurs first. Trained staff will assess patients twice daily to determine the presence or absence of delirium using the Confusion Assessment Method for the ICU score. Data will also be collected on demographics, the overall prevalence of delirium, duration and severity of delirium, sleep quality, participation in physiotherapy sessions, ICU and hospital LOS, morbidity and mortality, and healthcare costs. A subgroup of 100 patients will undergo polysomnographic testing to further evaluate the quality of sleep.

**Discussion:**

Delirium is a significant issue in ICU because of its frequency and associated poorer outcomes. This trial will be the largest evaluation of melatonin as a prophylactic agent to prevent delirium in the critically ill population. This study will also provide one of the largest series of polysomnographic testing done in ICU.

**Trial registration:**

Australian New Zealand Clinical Trial Registry (ANZCTR) number: ACTRN12616000436471. Registered on 20 December 2015.

**Electronic supplementary material:**

The online version of this article (doi:10.1186/s13063-016-1751-0) contains supplementary material, which is available to authorized users.

## Background

Delirium is a state of acute organic brain dysfunction with fluctuating disturbances of attention and cognition which occurs as a direct consequence of an underlying medical condition [1]. It is particularly common in patients in intensive care units (ICUs), with a wide range of prevalence ranging between 11% and 83% reported in the literature [2–5]. Researchers in a multi-centre study that included one of the participating hospitals of this trial reported a delirium prevalence of 45% [5], whereas a preliminary audit for this trial at the two primary sites demonstrated a delirium prevalence of 52% when evaluating patients with an expected ICU length of stay (LOS) of more than 24 h.

Delirium in intensive care is associated with worse outcomes. These include higher mortality (estimated as a 10% increase in the relative risk of death for each day of delirium) [6–10], more time on a ventilator [9–11], unplanned removal of tubes and catheters [10], increased use of physical restraints [11], increased requirement for tracheostomy, greater post-operative complications [12], poorer functional status, cognitive impairment [7, 9, 13, 14], increased hospital and ICU LOSs [8, 11, 12], increased medical costs [15], higher risk of dementia [7, 13] and greater likelihood of admission to residential care [7].

The aetiology of delirium is multi-factorial [16]. In the critical care setting, it is likely that disturbances of sleep and of the normal circadian rhythm play a significant role [17]. Sleep deprivation may occur as a result of environmental disturbances, loss of normal day-night routine, critical illness itself and patient treatments. However, although sleep disturbances have been demonstrated to predispose individuals to post-operative delirium, sleep problems and their relationship to delirium in ICU remain relatively unexplored [18, 19].

In the clinical setting delirium can be approached with prevention strategies or treatment strategies, with the former appearing to be more effective. Authors of a recent meta-analysis [20] reported 8 of 15 preventative studies were successful, compared with 1 of 10 treatment studies, in terms of reducing delirium incidence and duration. There are several non-pharmacological strategies used for preventing delirium in ICU, but there are no pharmacological strategies that are used routinely [6, 20]. Reasons for this include a lack of clear evidence, limited pathophysiological understanding, potential side effects, cost and difficulties identifying which patients will benefit [21, 22].

Good-quality sleep at night is rapidly being recognised as an important aspect of delirium prevention [19]. Melatonin is a natural hormone secreted by the pineal gland, which helps in the regulation of the sleep-wake cycle [23]. It is stimulated by low light, peaking during the main sleep period [24–26]. Melatonin can be given exogenously. In healthy volunteers, it decreases sleep onset latency, increases sleep efficiency and increases total sleep duration [27]. It also increases the duration of rapid eye movement (REM) sleep, which is thought to have a positive effect on health and healing [28]. It is inexpensive, has an excellent safety profile and is widely used in the community [29–31]. Critical illness causes deregulation of melatonin secretion by the pineal gland, and light and darkness fail to restore its normal pattern of secretion [32, 33]. Serum melatonin levels are found to be lower after surgery, in delirious post-surgical patients and in those receiving opioids [25, 34]. Studies have also demonstrated that exogenous melatonin is well absorbed enterally in critically ill patients [35].

Melatonin has previously been evaluated for the treatment of delirium, but only five trials have put it to the test as a prophylactic agent. Sultan and colleagues [36] evaluated prophylactic melatonin in patients requiring elective hip replacement surgery and found a significant decrease in delirium in the group receiving melatonin. Al-Aama and colleagues [37] compared prophylactic melatonin with placebo in a population of acutely ill elderly patients and found that melatonin was associated with a reduction in the incidence of delirium. De Jonghe and colleagues [38, 39] evaluated the effect of prophylactic melatonin versus placebo on the incidence of delirium in patients requiring hip surgery and found no significant difference. Hatta and colleagues [40] compared the melatonin receptor agonist ramelteon prophylactically with placebo in critically ill medical patients and found a significant reduction in delirium in the ramelteon group. Artemiou and colleagues [41] evaluated the use of prophylactic melatonin in patients undergoing cardiac surgery. They reported a delirium incidence of 8.4% versus 250 control patients in whom the incidence was 20.8%. However, there was no placebo in their trial, and the trial was not blinded.

### Rationale for proposed study

Delirium is common in ICU; it is associated with worse outcomes when it occurs; and currently there are limited therapies to prevent it. The studies evaluating melatonin as a prophylactic agent suggest that melatonin could play an important role in preventing delirium in the critically ill [19]. However, these studies were small and conducted with populations that do not include ICU patients. It is unclear whether these proposed benefits would be replicated in an adequately powered, randomised controlled trial or if they would translate to critical care. In the present study, we will attempt to answer the question whether, in a population of critically ill adults, prophylactic melatonin, compared with placebo [42], decreases the prevalence, duration and severity of delirium.

### Objectives

The primary objective of this trial will be to determine whether melatonin given prophylactically decreases the prevalence of delirium in critically ill patients. The secondary objectives will be to determine whether prophylactic melatonin decreases the severity and duration of delirium, improves sleep quality, reduces hospital and ICU LOS, improves morbidity and mortality, and reduces healthcare costs through reduced LOS and intensity of medical therapy.

### Trial design

This study will be a prospective, multi-centre, randomised, placebo-controlled, double-blind, prophylactic intervention trial of melatonin 4 mg versus placebo given at 21:00 for 14 days or until ICU discharge to critically ill patients admitted to ICU with an expected ICU LOS of at least 72 h (two arms, 1:1 allocation, parallel design). A subgroup of 100 patients from the two main research sites (Sir Charles Gairdner Hospital and John Hunter Hospital) will also undergo polysomnographic testing.

## Methods

### Participants and settings

This study will be conducted in closed ICUs of participating hospitals in Australia. ICUs currently involved are all in university-affiliated teaching hospitals. We will recruit 850 patients admitted to ICU with an expected LOS of at least 72 h.

### Eligibility criteria

#### Inclusion criteria

Patients admitted to a participating ICU identified by the treating intensivist as having an expected total ICU LOS of 72 h or more are eligible. Patients must be enrolled within 48 h of their ICU admission and receive the first dose of the study drug on the day of enrolment.

#### Exclusion criteria

The exclusion criteria are patients younger than 18 years of age; patients already receiving melatonin therapy before their admission to ICU; prior hypersensitivity reaction to any of the components (sucralose and glycerol) of the study drug; patients expected to be discharged within 72 h of admission; expected/inevitable death within 48 h of enrolment; pregnancy or breastfeeding; patients who are non-English-speaking; patients whose condition is not expected to improve adequately for them to be able to be assessed with a Confusion Assessment Method for the ICU (CAM-ICU) score during their ICU stay; patients who are not able to be assessed because of neurological problems that would affect their ability to participate in CAM-ICU assessment (as judged by the treating physician); no enteral route/nil by mouth (melatonin is not available in intravenous formulation); and hepatic impairment, defined as alanine aminotransferase greater than 500 IU/L, previous liver transplant or liver cirrhosis of Child-Pugh classes B and C.

### Interventions

Eligible participants will be randomised to receive melatonin 4 mg or placebo at 21:00 for 14 consecutive nights or until ICU discharge, whichever occurs first. This will be given either orally or via nasogastric tube, depending on the circumstances. All concomitant care and interventions that are normal practice for the ICU or based on other trials are permitted.

A subset of 100 patients will also undergo two episodes of polysomnographic testing overnight on days 2–3 and days 5–7 of their ICU stay. This will occur only at the two primary sites: Sir Charles Gairdner Hospital and John Hunter Hospital.

### Outcomes

All assessors using the CAM-ICU and the Confusion Assessment Method for delirium severity (CAM-S) will receive training in these assessment tools along with regular monitoring to ensure the tools are being applied reliably. The primary outcome will be prevalence of delirium. This will be measured and reported as delirium-free assessments. The secondary outcomes will be (1) overall prevalence of delirium, (2) duration of delirium, (3) severity of delirium, (4) sleep quality, (5) ICU and hospital LOS, (6) morbidity and mortality and (7) healthcare costs.

#### Prevalence of delirium

The primary outcome will be the proportion of delirium-free assessments as measured by the CAM-ICU score. Prevalence rather than incidence has been chosen because delirium on admission to ICU may not be measureable, owing to many patients being intubated and sedated and therefore unable to be assessed. Where possible, we will measure baseline delirium and provide an incidence in those patients. The CAM-ICU is widely used and is the best-performing of the tools adapted for use in ICU by non-psychiatrists, with a pooled sensitivity of 80.5% and specificity of 95.9% [43, 44]. The CAM-ICU will be used twice daily with all assessable patients while they are receiving the study drug for 14 days or until ICU discharge, whichever occurs sooner.

Secondary outcomes will include the following:

1. *Overall prevalence of delirium*: Patients will be diagnosed as delirious when they have at least one positive CAM-ICU up to ICU discharge or day 14 after enrolment if still in ICU.

2. *Duration of delirium*: Once the diagnosis of delirium is made, duration will be recorded as how many subsequent days on which they have a positive CAM-ICU until ICU discharge or day 14 after enrolment.

3. *Severity of delirium*: Severity will be assessed using the CAM-S Short Form [45], which gives a score from 0 to 8. Considering that sleep is an important part of this study, an additional question from the CAM-S Long Form on the sleep-wake cycle has been included in the assessment. Thus, a score from 0 to 10 will be recorded.

Indirect markers of delirium severity will also be recorded daily until ICU discharge or day 14 after enrolment. These are (1) need for anti-psychotics or sedation (total daily doses will be calculated); (2) need for physical restraints; (3) patient participation in physiotherapy sessions and mobilisation; and (4) patient removal of intravenous lines, drains or catheters.

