### Participant timeline and recruitment

Patients will be screened on the morning handover for eligibility. Baseline data will be recorded on day 0. Patients will be assessed each day and have the primary and secondary outcomes recorded daily until ICU discharge or day 14 after enrolment. Patients will be seen on the ward between days 2 and 14 after ICU discharge to complete the sleep questionnaire. Patients who have been discharged home will be contacted by phone. Patients will be followed through their hospital stay to record ICU LOS, hospital LOS, and 28- and 90-day mortality. The trial assessment schedule is displayed in Table 1 and Fig. 1.

**Table 1 Tab1:** Time schedule of Pro-MEDIC enrolment, interventions and assessments

	Day 1	Day 2	Day 3	Day 4	Days 5–14	Days 2–14 post-ICU discharge	Hospital discharge	Days 28 and 90
Inf`ormed consent	X							
Demographic information	X							
Medical co-morbidities	X							
Psychiatric history	X							
Liver function tests	X				X (days 0, 5 and 10)			
CAM-ICU score	X	X	X	X	X			
CAM-S test (for patients found to be delirious)	X	X	X	X	X			
Record daily ICU interventions	X	X	X	X	X			
Record daily anti-psychotic and sedation use	X	X	X	X	X			
Record daily sleep aid measures	X	X	X	X	X			
RCSQ	X	X	X	X	X			
Use of physical restraints	X	X	X	X	X			
Physiotherapy participation	X	X	X	X	X			
Polysomnography		X			X			
Assessment of sleep quality						X		
ICU and hospital LOS							X	
Hospital discharge destination							X	
Mortality at 28 and 90 days								X

*Abbreviations: CAM-ICU* Confusion Assessment Method for the ICU, *CAM-S* Confusion Assessment Method for delirium severity, *ICU* Intensive care unit, *LOS* Length of stay, *Pro-MEDIC* Prophylactic Melatonin for Delirium in Intensive Care, *RCSQ* Richards-Campbell Sleep Questionnaire

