### Sample size

On the basis of two sample size calculations, with an alpha value of 0.05 and a power of 80%, a total of 850 patients will be recruited into the study, with 425 patients in each arm. Estimates of sample size were made on the basis of percentage of delirium-free assessments (the primary outcome). An audit of 100 patients at Sir Charles Gairdner Hospital and John Hunter Hospital was used to obtain preliminary data to guide sample size calculations where an average of 54% of assessments were deemed delirium-free (SD 45%). The research group is aiming to detect a 10% increase in the percentage of delirium-free assessments. This would give us a sample size calculation of 319 per group. Adjustment for a non-parametric test (15%) increases this to 367 per group. It is expected that up to 10% of patients recruited into the study will not be assessable for delirium at any point during the study. To account for this and for missing data/loss to follow-up, the sample size was increased by 15% to 423 patients per group (total rounded to 850). This sample size will also be sufficient to analyse the secondary measures.

To prevent and treat the issue of likely missing data, the follow-up period for the primary outcome is short and data collection is electronic, with out-of-range and missing alerts. There will be documentation of why data are missing. This will help us to formulate reasonable assumptions about observations that are missing [48]. To achieve adequate recruitment numbers, there will be frequent reminders to the participating sites, and progress reports will be scheduled periodically.

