### Data collection and management

Data will be collected and entered into a REDCap© [49] electronic database behind a secure firewall. The REDCap system will perform data entry validation. For the non-primary sites, data can be entered into the REDCap database, or the case report forms can be filled in manually and forwarded to the primary sites. Strict confidentiality and privacy will be kept at all times. The data will be stored in password-protected files and will be kept for 15 years. The final database will be locked after all information for the last patient has been entered and provided to the statistician.

If a participant withdraws consent, the investigators will ask permission to retain all data collected up to the point of withdrawal and to collect survival status and discharge destination data. If subjects cease the study drug for any reason, data will still be collected and interpreted in an intention-to-treat analysis. The reason for withdrawal will be recorded. No attempt will be made to replace patients who withdraw from the study.

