### Statistical methods

Analyses will be conducted on both intention-to-treat and per-protocol bases. All outcomes will be analysed for superiority (two-sided) and considered statistically significant at the 5% level. Baseline data will be recorded and analysed for imbalances between the treatment groups. The primary endpoint, percentage of delirium-free assessments, will initially be analysed using a Mann-Whitney *U* test to compare the two treatment arms. Subsequent supporting analyses will be carried out using a negative binomial model with adjustments made for number of assessments (accounting for withdrawals), important covariates and baseline data where appropriate. Secondary endpoints of any prevalence of delirium during the 14 days and duration of delirium from first onset will be analysed using a chi-square test with supporting analyses of binary and ordinal logistic regression, respectively, allowing adjustments for covariates. Sleep quality analysis based on the Richards-Campbell Sleep Questionnaire on each of days 2–14, the patient-rated sleep questionnaire completed after day 14, and sleep measurements derived from polysomnography done on days 2–4 and 5–7 (total sleep time, sleep efficiency, REM sleep percentage and arousal index) will all be analysed initially using a Mann-Whitney *U* test to compare the two treatment arms and subsequently using linear mixed models with fixed factors of treatment time and their corresponding interaction, along with random patient effects. ICU LOS, total hospital LOS, mortality and morbidity events will be analysed initially using Kaplan-Meier curves and log-rank tests and subsequently using Cox proportional hazards models. Individuals withdrawn from the study early will be censored at the date of withdrawal. Specific subgroup analysis of major outcomes will be carried out, stratifying by age, sex, delirium medical subgroup and delirium risk as per the prediction of delirium in ICU patients (‘PRE-DELIRIC’) score. A fully specified statistical analysis plan will be finalised and approved by statisticians at the two main hospitals before the database is unlocked and opened. Data analysis is to be carried out using the R software programme [50].

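### The CAM-ICU sentence ties primary-outcome assessment to receiving study drug, against the protocol's own follow-up rules; separately, the primary percentage gives coma and death no value

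*Protocol article*

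**What the plan says.** The primary endpoint is defined under *Prevalence of delirium*: "The primary outcome will be the proportion of delirium-free assessments as measured by the CAM-ICU score". The same section says who is assessed and when: "The CAM-ICU will be used twice daily with all assessable patients while they are receiving the study drug", with an upper limit of 14 days or ICU discharge.

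Other sections describe follow-up without an on-drug condition:

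- *Data collection and management*: "If subjects cease the study drug for any reason, data will still be collected and interpreted in an intention-to-treat analysis".
- *Participant timeline and recruitment*: "Patients will be assessed each day and have the primary and secondary outcomes recorded daily until ICU discharge or day 14 after enrolment". Table 1 there schedules the CAM-ICU on every column from day 1 to days 5–14.
- *Prevalence of delirium*, secondary outcomes 1 and 2: overall prevalence and duration use CAM-ICU results up to ICU discharge or day 14.
- *Statistical methods*: "Analyses will be conducted on both intention-to-treat and per-protocol bases".

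On unassessable patients, *Sample size* expects that "up to 10% of patients recruited into the study will not be assessable for delirium at any point during the study" and enlarges the trial for this and for missing data. *Statistical methods* tests the percentage by Mann-Whitney. A negative binomial model adjusted for number of assessments serves as supporting analysis.

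**The concern.** There are two separate issues.

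The first is the on-drug phrase. The article foresees stopping the drug early: *Allocation, randomisation, compliance and blinding* says adverse events may lead to this, and the drug has an enteral form only. If site staff follow the CAM-ICU sentence as written, a patient whose drug is stopped is no longer assessed for the primary outcome. The intention-to-treat analysis would then rest on on-drug data, and no later analysis plan could restore what was not collected.

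The second is the denominator. The percentage is taken over assessments that could be made, so coma, deep sedation and time after death drop out. Assessability arises after randomisation, and treatment may affect it. The article says sedated patients cannot be assessed, lists need for sedation among its indirect markers of delirium severity, aims to reduce severity, and leaves sedative use unrestricted. If the arms differ in assessability or early death, the percentages are compared over differently selected time.

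**Working it through.** **1. The passages side by side.**

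| Place | End of CAM-ICU or primary-outcome data | On-drug condition |
|---|---|---|
| *Prevalence of delirium*, CAM-ICU sentence | 14 days or ICU discharge | Yes |
| *Prevalence of delirium*, secondary outcomes 1 and 2 | ICU discharge or day 14 | No |
| *Participant timeline and recruitment* | ICU discharge or day 14 | No |
| *Data collection and management* | Continues after drug stops | No |

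The rows agree while the drug continues. They differ only for a patient whose drug stops before ICU discharge and before day 14.

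**2. The plan's own sample size.** Inputs from *Sample size*: difference 10 points, SD 45 points, two-sided alpha 0.05, power 80%.

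- 2 × (1.960 + 0.842)² × 0.45² / 0.10² = 318 per group by the normal approximation; the t-test version gives 318.8, so 319.
- 319 × 1.15 = 366.9, so 367.
- 367 × 1.15 = 422.05, so 423 per group; 2 × 423 = 846, rounded to 850.

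The stated figures reproduce, and this point does not change them. The never-assessable allowance is at most 0.10 × 850 = 85 patients.

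**3. What the percentage does for one patient.** Two assessments a day for 14 days give 28 slots.

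| Course | Primary percentage | Clear assessments out of 28 |
|---|---|---|
| 28 clear | 28/28 = 100% | 100% |
| 8 clear, comatose or dead for the other 20 | 8/8 = 100% | 8/28 = 29% |
| 4 clear, then death | 4/4 = 100% | 4/28 = 14% |
| 2 clear, then death | 2/2 = 100% | 2/28 = 7% |

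All four tie at the top rank in the Mann-Whitney test. The last column only shows what the percentage leaves out. It is not proposed as an endpoint, since it would also penalise early live discharge.

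**4. Size of a between-arm artefact (hypothetical).** The documents give no rates of coma, death or drug cessation by arm, so every input below except the 54% is an assumption. There is no true effect on delirium.

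(a) A share x of delirious assessments is lost in one arm only. That arm shows 0.54 / (0.54 + 0.46 × (1 − x)).

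| x | Arm shows | Shift |
|---|---|---|
| 0 (or equal loss in both arms) | – | none between arms |
| 5% | 55.3% | +1.3 |
| 10% | 56.6% | +2.6 |
| 20% | 59.5% | +5.5 |
| 30% | 62.6% | +8.6 |

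About 34% would have to be lost to create the full 10 points.

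(b) The opposite direction: 30 of 100 slots are unassessable in control, so 0.54 × 70 = 37.8 are clear. Treatment makes k more slots assessable, of which a fraction f is clear. The treated arm shows (37.8 + k × f) / (70 + k).

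| k | f | Arm shows | Shift |
|---|---|---|---|
| 5 | 0.40 | 39.8/75 = 53.1% | −0.9 |
| 10 | 0.40 | 41.8/80 = 52.3% | −1.8 |
| 5 | 0.20 | 38.8/75 = 51.7% | −2.3 |
| 10 | 0.20 | 39.8/80 = 49.8% | −4.2 (−4.25 unrounded) |
| any | 0.54 | 54.0% | 0 |

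Both tables pool slots, whereas the planned test ranks one percentage per patient. They show direction and order of size, not the shift in the tested quantity.

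**The case against.** **The on-drug phrase may be loose wording.** *Interventions* gives the planned treatment as "melatonin 4 mg or placebo at 21:00 for 14 consecutive nights or until ICU discharge, whichever occurs first", the same window as the CAM-ICU sentence, so the phrase may only describe that window. This stands as a reading, and a reader should not infer that the primary outcome is established as on-drug only. It does not remove the need to correct the sentence, because it is the one that tells staff when to assess.

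**The assessable-only rule does not breach intention to treat.** A reader might infer that it does. It does not: a comatose patient cannot be scored under any analysis set. Only the on-drug phrase conflicts with the intention-to-treat statement. The denominator is a limitation of the endpoint definition.

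**The article already mitigates part of this.** It excludes patients not expected to become assessable or expected to die within 48 h of enrolment, enlarges the sample, documents reasons for missing data, adjusts a supporting model for number of assessments, and reports mortality and ventilator-free days separately. The monitoring committee reviews unblinded data. A harmful effect on mortality would therefore not go unseen. But a larger sample restores numbers, not comparability; the supporting model gives coma and death no value; and separate mortality reporting leaves the primary test as it is.

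**The SAP may deal with coma and death.** It is not shown, so the absence of such handling from the article is not held against the plan. What is raised is the primary percentage as the article fixes it.

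**No differential loss is shown.** This is correct. The trial is double-blind, and equal loss creates no between-arm difference under the null.

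**Conclusion.** The point holds in two parts of different strength.

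The wording conflict is firm. Read literally, the CAM-ICU sentence contradicts *Data collection and management*, *Participant timeline and recruitment* and the secondary outcomes in its own section. The number of patients affected cannot be computed, because the article gives no rate of early drug cessation. The loss would be irrecoverable and recruitment is under way, so the passages should be reconciled promptly.

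The denominator is a real limitation of unknown size. It leaves at most 85 of 850 patients without a value and lets very short, clear records score 100%. Bias requires assessability or death to differ by arm, which the article's own reasoning makes plausible but which nothing shows or excludes. A reader might take one worked figure, such as 4.2 points, as the expected bias. It is not: it rests wholly on assumed inputs, and under the assumptions tried the shift runs from −4.2 through zero to +8.6 points. The sample size is unaffected.

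**What to change.** 1. Reword the CAM-ICU sentence so that assessable patients are assessed twice daily until ICU discharge or day 14 after enrolment, whether or not study drug continues. This matches the other sections and concerns data collection only, not when the drug should be stopped. Cost: one sentence, a note to sites, and assessments that the other sections already require.

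2. Keep the primary endpoint and sample size. Pre-specify one supporting analysis on all randomised patients, such as days alive and free of delirium and coma to day 14. Days dead or wholly unassessable count as not free, and days after live ICU discharge count as free, with a sensitivity analysis on that last rule. Cost: one more analysis. It answers a somewhat different question, days after ICU discharge are not observed, and days unassessable for benign reasons count against the patient.

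3. Report by arm the number of unassessable slots and of never-assessable patients. The planned record of reasons for missing data should largely supply this.

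4. Label any numerical illustration of bias as hypothetical and show it as a range over its assumed inputs.
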